#### Definition of analysis population {27b}

Following the intention-to-treat principle, participants will be analysed according to the assigned intervention arm, disregarding actual compliance with the assigned intervention. Furthermore, in inspecting the robustness of the noninferiority outcomes, supportive sensitivity analyses are carried out per-protocol, meaning only participants who did not drop out of the assigned intervention are included.

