##### Generalist condition (GIT-PD)

 Level of Speciality: GIT-PD is a non-theoretical and non-methodological approach without a specific theory of aetiology for PD. Rather, GIT-PD builds upon treatment as usual and improves regular care by implementing a framework of common factors derived from evidence-based treatments for PD [31]. These common factors include basic skills to build a relationship (empathy, positive regard, authenticity), to address ruptures, to reach consensus on goals and tasks, and to increase (affective) self-reflection and expression of emotions, inviting the application of a wide array of therapeutic techniques with varying aetiological backgrounds (e.g. behavioural, cognitive, psychodynamic) directed at goals of the individual patient. GIT-PD focuses on 1) an engaging, validating, curious and authentic/transparent therapist stance; 2) common factors like a) therapist relationship and repair of ruptures in the alliance; b) motivation and expectancy for change; c) emotion regulation; d) self-reflection; 3) improving team functioning by targeting potentially harmful team processes and by increasing an open and transparent discussion and collaboration; 4) institutional embedment including crisis pathways and close collaboration between different services; explicit managerial support is required as a context of peer-supervision and frequent mutual support between therapists is essential for its success. GIT-PD is manualised and has been implemented across more than 30 institutions, given its simple and straightforward approach to treatment.Format and Content of GIT-PD: GIT-PD consists of a structured pathway of episodes in treatment (assessment, middle, termination, booster) based upon a review of goals. GIT-PD assumes that, irrespective of PD type, all patients with PD share impairments in personality functioning as reflected in self and interpersonal impairments. GIT-PD is modularly designed. The structure of the GIT-PD programs includes: 1) an assessment phase including careful assessment, psycho-education, and discussion of diagnosis and case formulation; 2) a modular treatment phase, including group modules targeting core areas of PD, such as emotion regulation and interpersonal functioning; 3) additional personalised treatment modules that may include crisis planning, case management, trauma modules, family sessions and other problem-focused modules; 4) a follow-up phase with limited treatment focused at generalizing treatment benefits. Total treatment duration depends on specific patient needs but will usually vary between 12 and 18 months. GIT-PD may vary in format and content, allowing local variations to a certain extent. However, all treatments must be manualised, address specific problem areas of personality pathology, and aim at generalising treatment outcomes in daily life during the follow-up phase in order to prevent relapse and optimise participation in society again.Team discipline mix: GIT-PD is psychotherapeutically-informed. In daily practice, treatment is supervised by licensed psychotherapists, healthcare psychologists, clinical psychologists or psychiatrists and mainly delivered by other disciplines, like psychiatric nurses, social workers and Master’s level psychologists. Training is accessible to a broad range of disciplines, too.Required level of training and supervision of individual therapists: GIT-PD requires a two-day team training. Team supervision within teams will be organised according to the GIT-PD guidelines.Dosage and duration of treatment: GIT-PD has a flexible approach, enabling tailoring treatment to the clinical needs of different types of patients. The treatment duration (start-end) is 12- 18 months on average.

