
#### Criteria for discontinuing or modifying allocated interventions {15b}

The sponsor will suspend the study if there is sufficient ground that continuation of the study will jeopardise participant health or safety. Suspension is deemed unlikely as this study only includes regular treatment programs that have already been implemented and sustained at these sites in the Dutch mental health care system. Therapeutic progress is evaluated throughout the allocated treatment. If the therapist deems it necessary to modify the treatment, push the participant out of the allocated treatment or cross the participant over to the alternative treatment arm, then this decision needs to be discussed with the therapist in the Trial Steering Committee. Furthermore, participants can decide to discontinue the allocated treatment if desired.

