#### Relevant concomitant care permitted or prohibited during the trial {15d}

Co-interventions are not offered as part of the study. Participants are, however, not explicitly prohibited from seeking additional care if desired. However, Dutch healthcare insurances cover only one PD treatment at a time. Participants are prohibited from receiving the interventions of the condition that was not allocated during randomisation for the duration of the trial.

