### Ancillary and post-trial care {34}

The studied interventions are standard treatments within the participating Dutch mental healthcare institution. Therefore, participation does not involve additional risks, and therapeutic progress is reviewed collaboratively between the participant and therapist throughout the treatment. After completing the allocated treatment, participants can seek follow-up care if desired. However, the participant’s respective institution is not allowed to provide care of the opposite treatment arm for the duration of the trial, unless explicit permission is sought and obtained from the TSC. Dropping out of the study will not affect the treatment provided. If participants discontinue the allocated treatment, they will still be assessed and included in the analysis according to the intention-to-treat principle, unless consent is withdrawn.

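### The per-protocol set is defined only by not dropping out, so it keeps generalist completers who receive specialist care before T4, and the crossover rules conflict

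*Protocol article*

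**What the plan says.** Section {27b} makes intention-to-treat the main analysis: "participants will be analysed according to the assigned intervention arm, disregarding actual compliance with the assigned intervention". For robustness it adds per-protocol sensitivity analyses in a supportive role, "meaning only participants who did not drop out of the assigned intervention are included". No other condition on the per-protocol set is stated.

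Section {27c} plans two further sensitivity analyses of the primary analyses, multiple imputation and complete case, both about missing data. Section {27d} says nothing else is planned. Section {5} says that the statistical analysis plan is available in this publication.

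On generalist treatment the intervention description says: "The treatment duration (start-end) is 12- 18 months on average". The Discussion fixes the primary endpoint (T4) at 18 months after treatment start in both arms.

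Three sections deal with opposite-arm care:

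- {15d}: "Participants are prohibited from receiving the interventions of the condition that was not allocated during randomisation for the duration of the trial".
- {15b}: if the therapist finds it necessary to "cross the participant over to the alternative treatment arm, then this decision needs to be discussed with the therapist in the Trial Steering Committee".
- {34}: completers may seek follow-up care, but their institution may not give opposite-arm care during the trial "unless explicit permission is sought and obtained from the TSC".

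**The concern.** In a non-inferiority trial, specialist care that reaches the generalist arm pulls the two arms together and so favours the hypothesis under test. Intention-to-treat ignores this by design. A per-protocol analysis is the usual place to see whether the conclusion survives once such cases are set aside. Here the set is defined by drop-out alone. A participant who finishes the generalist programme and then moves to specialist care has not dropped out, so the analysis meant to expose contamination keeps it.

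The conflicting crossover rules add to the problem. Without one rule it is unclear which opposite-arm care is a protocol deviation and which is permitted care, and a per-protocol definition needs that distinction.

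**Working it through.** **Who stays in the set.** A generalist participant completes at 12 months. Up to 18 − 12 = 6 months remain before T4. With steering committee permission under {34}, specialist care starts in that window. The participant did not drop out, so the {27b} criterion is met and the T4 score counts as a per-protocol generalist outcome.

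**The three crossover rules side by side.** {15d} prohibits opposite-arm care for the whole trial and names no exception. {15b} envisages a crossover after discussion in the steering committee and does not mention approval. {34} requires the committee's permission and addresses the participant's own institution. Prohibition, discussion and permission are three different conditions.

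**The plan's own figures.** 316/0.883 = 357.87, so 358 is reproduced exactly. The 316 came from simulation. An approximation with a linear slope, correlation 0.50 and seven equally spaced measurements gives a variance of total change of 0.5 × 36/28 = 0.643. Then n = 2 × 0.643 × (1.960 + 0.842)²/0.25² ≈ 162 per group, within 3% of the stated 158. The actual month spacing gives 151. The standard error implied by 80% power at the margin is 0.25/(1.960 + 0.842) = 0.0892.

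**Illustration of dilution.** The documents give no crossover rate, so these inputs are assumed. Let c be the share of the generalist per-protocol set that receives specialist care before T4, and f the share of the deficit this recovers. With a true deficit at the margin:

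- expected per-protocol difference = −0.25 × (1 − c·f)
- P(non-inferiority declared) = 1 − Φ(1.960 − 0.25·c·f/SE)

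For a per-protocol set of 80% of the planned size, SE = 0.0892/√0.8 = 0.0998.

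| c·f | Expected d | False NI, SE 0.0892 | False NI, SE 0.0998 |
|---|---|---|---|
| 0 | −0.25 | 2.5% | 2.5% |
| 0.05 | −0.2375 | 3.4% | 3.3% |
| 0.10 | −0.225 | 4.7% | 4.4% |
| 0.20 | −0.20 | 8.1% | 7.2% |

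A c·f of 0.10 means 10% crossing over with full recovery, or 20% with half recovery.

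**Sensitivity to the standard error.** The first-ranked outcome, the STiP-5.1, has only two time points in the primary model. With correlation 0.5 and 158 per group, a baseline-adjusted comparison has SE = √(2 × 0.75/158) = 0.097. At c·f of 0.10 and 0.20 this gives about 4.4% and 7.4%. A simple change score has SE = √(2/158) = 0.113 and gives about 4.1% and 6.5%. The order of magnitude does not change.

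**What exclusion can do.** Suppose a share c is excluded and, without specialist care, would have scored x SD below the generalist arm mean. The mean of those left rises by c·x/(1 − c). With c = 0.10 and x = 0.225 the shift is 0.1 × 0.225/0.9 = 0.025 SD. That equals the dilution from retaining them with full recovery, and has the same direction. With c = 0.20 the break-even is x = 0.20 (0.2 × 0.20/0.8 = 0.05 SD).

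**The case against.** The strongest reply is that the affected group is small. Opposite-arm care is barred by default. A participant crossed over during treatment leaves the assigned intervention and would plausibly count as a drop-out, so is already excluded. What remains is an early generalist completer who gets specialist care by exception and benefits before T4. The Discussion describes long waiting lists. Specialist programmes need at least 40 sessions or 12 months, so at most about half of a 12-month programme fits into six months. This stands: the cases are exceptions of unknown number, and the illustration cannot be read as a forecast.

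It can also be said that {15d} states a default and {15b} and {34} its exceptions. That is a reasonable guess at the intent, but {15d} admits no exception, and {15b} and {34} set different conditions for one. Conversely, a reader might infer from {34} that care at another institution is unrestricted. {15d} does not support that, because it binds the participant without reference to institution.

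Two objections to a simple exclusion rule also stand. Generalist completers who are granted specialist care are plausibly poor responders, so removing them can itself favour non-inferiority. In addition, the data are not shown to be in hand. Under {15c}, file data on duration, minutes and sessions are taken at completion or drop-out. The TiC-P recalls three months, while T3 to T4 spans six.

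The point is not simply detail left to another document: {27b} states a definition, and it is that definition which lets these cases through.

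**Conclusion.** The point holds in a limited form. As worded, the only adherence-related sensitivity analysis keeps generalist completers who receive specialist care before T4, and this biases it toward non-inferiority. The sections on opposite-arm care contradict each other and must be reconciled. Which rule should apply is not for a statistical review to say.

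The size cannot be derived from the documents. The illustrative 3.4% to 8.1% assumes a true deficit at the margin, effective dilution of 5% to 20%, crossing participants who otherwise resemble the rest of the arm, and the standard error implied by the planned sample size. A smaller per-protocol set gives slightly lower figures.

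Three stronger readings are not supported:

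- That this is the trial's only robustness check. Section {27c} plans two more, though both concern missing data.
- That the trial's own error rate rises to 8%. The trial conclusion rests on the intention-to-treat fixed sequence in {27a}, and the per-protocol analysis is supportive.
- That crossover will be common. Nothing in the documents suggests a rate.

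**What to change.** Keep intention-to-treat as the primary analysis. In {27b}, define the per-protocol set as participants who started the allocated programme, did not drop out, and received no opposite-arm intervention before T4, including any permitted by the steering committee. Naming the start of treatment also settles the status of those who never began. Determine membership blind to outcome.

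Reconcile {15b}, {15d} and {34} so that they state one rule. Log each crossover permitted by the steering committee with its date, and check the patient file at T4 for opposite-arm care.

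Report the number excluded per arm. Show the per-protocol result both with these participants excluded and with them retained, because either choice alone can lean toward non-inferiority.

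The cost is a few sentences, a dated log and a small amount of extra record checking. The downsides are a slightly smaller per-protocol set and possible selection bias from the exclusion, which the paired presentation makes visible. Enrolment is expected to run to the end of 2026, so the change can be made before T4 data are analysed.

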#### How missing data will be handled in the analysis {27c}

The multi-level mixed-effects models allow for incomplete outcome data, while assuming Missing at Random (MAR). The actual missingness mechanism is, however, unknown. This will be examined by comparing baseline characteristics between participants with and without missing outcome values. Furthermore, to examine the influence of missingness on the primary analyses, two sensitivity analyses are performed; the first repetition of the primary analyses will additionally use multiple imputation through predictive mean matching to impute the missing values on the repeated measurements of the dependent variable. The second repetition will cover a complete case analysis, including only the participants without missing data on the respective primary outcome.

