### Sample size {19}

The required sample size was determined using a computer simulation. Twenty-one thousand datasets with varying sample sizes were simulated for an RCT design with seven repeated measurements on a continuous outcome variable, where both interventions exhibit equal improvement over time. The outcome measures were assumed to follow a multivariate normal distribution in both groups, with a repeated measures correlation of 0.50 and a decrease of *d* = 0.30 in both groups across the seven repeated measurements. Each of these datasets was analysed using a longitudinal multilevel model (see *Statistical methods for primary and secondary outcomes, including harms {27a}).* Subsequently, in each dataset, it was tested whether generalist treatment is non-inferior to specialist treatment by examining whether the lower limit of the two-sided 95% confidence interval of the difference between treatments in improvement over time is greater than the non-inferiority limit of *d* = 0.25. It was found that with this design, 316 participants are necessary (158 per group) to test non-inferiority with a power of 0.80 and α = 0.025. To account for attrition, which we estimate at 11.7% for the primary endpoint (T4) based on a similar study [19], the complete sample needs to consist of (316/0.883 = 357.87) 358 participants. This comes down to 179 participants per treatment condition.

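### No planned analysis departs from missing at random, and for the two-point STiP-5.1 the complete-case repetition essentially equals the primary analysis

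*Protocol article*

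**What the plan says.** In section {27c} on missing data, the multilevel models "allow for incomplete outcome data, while assuming Missing at Random (MAR). The actual missingness mechanism is, however, unknown". The plan's check on the mechanism is this: "This will be examined by comparing baseline characteristics between participants with and without missing outcome values". It then repeats the primary analyses twice to gauge the influence of missingness. The first repetition uses "multiple imputation through predictive mean matching to impute the missing values on the repeated measurements of the dependent variable". On the other it says: "The second repetition will cover a complete case analysis, including only the participants without missing data on the respective primary outcome".

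Section {27b} adds a per-protocol analysis, "meaning only participants who did not drop out of the assigned intervention are included". Section {27d} states that nothing beyond the analyses already named is planned. Item {5} of the administrative table places the statistical analysis plan in this article, and partly in the ethics-approved protocol.

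Section {27a} fits the STiP-5.1 at two time points and the LPFS-BF 2.0 at five. Each model is adjusted for the baseline value of its outcome and for no other covariate. The STiP-5.1 is tested first, and if it fails there is no trial-level non-inferiority. Section {19} allows for attrition, "which we estimate at 11.7% for the primary endpoint (T4) based on a similar study".

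**The concern.** The plan admits that it does not know why outcomes will be missing, and then chooses tools that cannot probe the assumption in doubt. Imputation by predictive mean matching relies on MAR, as the primary model does. Complete case does not relax that assumption. Comparing baseline characteristics shows whether missingness relates to what was measured at T0; it cannot show whether it relates to the unseen T4 score. The per-protocol analysis removes treatment drop-outs and so does not fill the gap.

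The weakness falls on the decisive test. In the two-point STiP-5.1 model, a participant without T4 has no post-baseline value, so leaving that participant out changes essentially nothing. In a non-inferiority trial, an unseen poor outcome concentrated in the test arm moves the estimate towards the claim. Similar primary and sensitivity results could then be read as robustness that was never tested.

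**Working it through.** **Plan's own figures.** Evaluable N is 316 (158 per arm) and attrition 11.7%: 316 / 0.883 = 357.87, giving 358 (179 per arm), as stated. About 0.117 x 179 = 21 participants per arm would lack T4. The 316 came from the authors' own simulation. A slope over seven equally spaced waves with correlation 0.50 gives 162 per arm, close to their 158.

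**Does complete case differ from the primary analysis for the STiP-5.1?** I compared maximum likelihood on both waves for everyone with baseline-adjusted regression on completers only, in 40 simulated data sets of 179 per arm with correlation 0.50. The largest gap in the treatment effect was 8e-8. The site level was left out, hence *essentially* equal.

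**Does imputation differ?** With baseline and arm as the only predictors, the imputed estimate differed from the primary one by 0.007 to 0.008 d on average (1,500 trials per scenario, 20 imputations). The plan does not list its predictors, so this is one possible case.

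**Size of a departure from MAR.** Let delta be how much worse, in SD, the missing outcomes in an arm are than MAR predicts.

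- Bias towards non-inferiority = (missing share in GIT-PD x delta GIT-PD) - (missing share in specialist x delta specialist). With 11.7% in each arm this is 0.117 x (delta GIT-PD - delta specialist).
- Standard error for a baseline-adjusted single follow-up, using the plan's correlation of 0.50 and 158 per arm: sqrt(2 x (1 - 0.50²) / 158) = 0.0974.
- False non-inferiority at a true difference of -0.25 = Phi(-1.96 + bias / 0.0974).

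The deltas are assumptions; the article gives none.

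| Delta GIT-PD | Delta specialist | Bias (d) | Share of margin | False non-inferiority |
|---|---|---|---|---|
| 0 | 0 | 0 | 0% | 2.5% |
| 0.5 | 0 | 0.059 | 23% | 8.7% |
| 1.0 | 0 | 0.117 | 47% | 22.4% |
| 0.5 | 0.5 | 0 | 0% | 2.5% |
| 0 | 0.5 | -0.059 | -23% | 0.5% |

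Equal deltas cancel only if drop-out is also equal. With 16% missing in GIT-PD, 7.4% in specialist and delta 0.5 in both, the bias is 0.16 x 0.5 - 0.074 x 0.5 = 0.043 and the error 6.4%.

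The result depends little on the standard error. The value implied by 80% power at a margin of 0.25 is 0.25 / (1.96 + 0.8416) = 0.0892. With it, the two GIT-PD-only rows become 9.6% and 25.8%.

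**Tipping point.** If the true difference is zero, the expected lower limit is -1.96 x 0.0974 = -0.191, which leaves 0.059 before -0.25. Then 0.059 / 0.117 gives a GIT-PD-only delta of about 0.50 SD. With standard error 0.0892 it is 0.075 / 0.117 = 0.64 SD.

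**Would the planned analyses warn of the problem?** In simulation, drop-out depended on the unseen T4 score in GIT-PD only (an assumed logistic form, 11.7% missing per arm, true difference -0.25). The mean estimates were -0.163 (primary and complete case) and -0.161 (imputed from baseline and arm). Both falsely declared non-inferiority in 15.7% of trials, against 2.5% with full data. Under MAR the rates were 2.6% and 2.7%. The analyses agreed equally well in both settings.

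**The case against.** **Auxiliary variables.** A reader might infer that primary, imputed and complete-case results must all agree by construction. The article does not support that for the imputation. Its predictors are unstated, and interim LPFS-BF 2.0 scores could move the result. It would still be a MAR analysis.

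**T6 data.** A reader might also infer that someone without a T4 STiP-5.1 has only T0 on that measure. That is true inside the two-point primary model only. Section {27a} uses three STiP-5.1 measurements in the long-term model, and section {25b} offers those thinking of leaving a reduced battery aimed at T4 and T6. A T6 score may exist and could inform imputation.

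**LPFS-BF 2.0.** With five waves, complete case is a distinct analysis, resting on a stronger assumption than the mixed model. The duplication concerns the STiP-5.1 alone.

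**Direction.** Nothing in the article says that informative drop-out will be worse in GIT-PD. The discussion expects a higher dosage in the specialist arm, so the reverse is not excluded. The 8.7% and 22% are adverse scenarios, not forecasts.

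**Retention.** Section {34} keeps assessing participants who stop treatment, so stopping treatment is not the same as a missing outcome. This reduces missing data but does not test MAR.

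**A condensed article.** A fuller plan could hold another analysis. But section {27d} closes the list and item {5} places the analysis plan here. The objection is to the methods this text chose for a stated purpose.

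**Conclusion.** The concern holds in this form: no planned analysis departs from MAR, the baseline comparison cannot detect missingness that depends on the unseen score, and for the STiP-5.1 gatekeeper the complete-case repetition adds essentially nothing. Agreement among the planned analyses would therefore not show that non-inferiority is robust to informative drop-out.

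The possible size is material but conditional. It rests on assumed deltas, 11.7% missing per arm, a two-wave standard error of 0.097 and a true difference at the margin. The effect runs from conservative to clearly anti-conservative according to which arm's drop-outs are worse. The article supports neither a claim that the trial will wrongly declare non-inferiority nor a claim that all three analyses must coincide. The plan should be changed, but the primary model need not be.

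**What to change.** Add to section {27c} a pre-specified delta-adjusted multiple imputation with a tipping point for T4 STiP-5.1 and T4 LPFS-BF 2.0:

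- Impute by arm, naming the auxiliaries, all of which are already collected: interim LPFS-BF 2.0 scores, T6 STiP-5.1 where available, baseline measures and treatment completion.
- Vary delta separately by arm over a grid fixed in advance (for example 0 to 1.0 SD in steps of 0.25). Include equal shifts, GIT-PD-only shifts and the reverse.
- Report the delta at which the lower confidence limit crosses -0.25, beside the observed missingness in each arm.

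Keep the complete-case analysis for the LPFS-BF 2.0 if wished, but do not present it as a robustness check for the STiP-5.1. Amend section {27d} to match.

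The cost is a little more analysis work and no new data. Data collection is expected to run until December 2029, so the grid can be fixed well before analysis. The downside is that the result may look less robust than three MAR-based analyses would suggest.
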